## Abstract

**Background:**

There is scarcity of trials about preventative strategies for low anterior resection syndrome (LARS) in rectal cancer patients. The aim of this study is to evaluate the effectiveness of a pre- and post-surgical pelvic floor rehabilitation program on the bowel symptoms, pelvic floor function, and quality of life of rectal cancer patients.

**Methods:**

A randomized controlled trial with parallel groups (pelvic floor rehabilitation versus control group), with a blinded evaluator. Participants and setting: 56 stage I to III rectal cancer patients aged from 18 to 80 years old undergoing sphincter preservation surgery at Hospital del Salvador and who have a sufficient knowledge of Spanish. Main outcome measures: ICIQ-B questionnaire for intestinal symptoms, high-resolution anorectal manometry (Alacer Multiplex 24-channel manometry equipment) for anorectal function, pelvic floor muscle strength test with Oxford Modified Scale, and a quality of life test with the EORTC QLQ C30 questionnaire. The evaluations will be carried out at five stages: before surgery, before and after the pelvic floor rehabilitation, and during a 3-month and 1-year follow-up. Interventions: one pre-rehabilitation session and 9 to 12 sessions of pelvic floor rehabilitation, including patient education, pelvic floor muscle exercises, pelvic floor electromyography biofeedback, and capacitive and sensory rectal training with a balloon probe. Rehabilitation will begin 3–5 weeks before the ileostomy is removed (four sessions) and around 3 weeks after stoma removal (5–8 sessions).

**Discussion:**

We expect the program to improve the bowel symptoms, pelvic floor function, and quality of life of rectal cancer patients.

**Trial registration:**

Australian New Zealand Clinical Trials Register ACTRN12620000040965. Registered on 21 January 2020.

## Introduction

### Background and rationale {6a}

Rectal cancer is a recognized health problem that compromises patients’ health-related quality of life. Worldwide in 2018, the incidence of rectal cancer was 3.9%, while its mortality rate was 3.2%, considering the total number of cancer cases [1]. Nevertheless, the prevalence of rectal cancer survivorship is increasing with the improvement of treatments, and surgery with radio-chemotherapies has significantly improved oncological outcomes [2]. In addition, the implementation of perioperative optimized protocol pathways has reduced rates of morbidity, improved recovery, and shortened the length of hospital stay [3].

Currently, surgeries for rectal cancer are less aggressive and try to preserve the anal sphincter and to avoid permanent ostomies [2]. Nevertheless, the partial or total loss of the rectal reservoir and its replacement with the remaining colon is associated with functional sequelae [4], triggering a negative effect on the pelvic floor region with compromises in evacuation and urinary function. This has been recently investigated and termed as “low anterior resection syndrome” (LARS) [4, 5].

LARS includes a set of symptoms, as well as frequent bowel movements, urgency, fecal incontinence, and disordered evacuation. It was estimated that this syndrome occurs in 70 to 90% of patients [4, 5]. Studies have shown that the main risk factors for developing LARS after surgery are radiotherapy and tumor height, which both have a negative impact on bowel function [6, 7]. LARS can show improvement over the first 2 years, but symptoms persist for longer than 2 years in nearly 60% of patients [8].

There are few studies testing interventions to improve bowel symptoms in patients treated for colorectal cancer, especially those who are submitted specifically to sphincter saving surgeries which are associated with LARS. One retrospective study showed the benefits of biofeedback with balloon rectal training on bowel function, measured with questionnaires and an anorectal manometry [9]. Another recent prospective study included patients who experienced fecal incontinence after sphincter-saving surgery and showed that electrical stimulation and biofeedback improved maximal squeeze pressure and stool frequency and diminished the use of antidiarrheal medications [10].

Two systematic reviews analyzed the effects of pelvic floor rehabilitation on the bowel function of rectal cancer patients after surgery. One of them identified that most studies reported significant improvements in stool frequency, incontinence episodes, severity of fecal incontinence, and patients’ health-related quality of life after pelvic floor training with pelvic floor muscle exercises (PFME) and biofeedback [11]. The other systematic review included studies that used multimodal pelvic floor rehabilitation—pelvic floor muscle training, rectal balloon training, and biofeedback—and showed an improvement regarding continence, stool frequency, and quality of life [12]. However, both systematic reviews concluded that their included studies had some methodological limitations, such as a lack of a non-exposed cohort, a lack of independent blinded assessment, heterogeneous treatment protocols, and a lack of long-term follow-up [11, 12]. So, there is a need for methodologically robust randomized controlled trials to test the effectiveness of pelvic floor rehabilitation with muscle training, balloon rectal biofeedback, and electrostimulation on bowel function and quality of life.

In addition, none of these studies addressed the benefits of delivering pelvic floor interventions prior to, as opposed to following, colorectal cancer treatments. Patients might benefit with one session of pelvic floor pre-rehabilitation including health education and teaching the exercise before surgery. Rehabilitation for cancer patients is a new field and is charged with providing care throughout the course of illness and wellness to maximize potential function and alleviate disability [13]. Recently, rehabilitation services have faced a paradigm shift from a restorative to a more prospective approach that aims at prevention and early intervention to mitigate the impact of disability [13]. Pre-rehabilitation of cancer patients refers to preventive rehabilitation interventions aiming to enhance patient’s functional capacity. It allows patients to better tolerate cancer treatments [14, 15].

### Objectives {7}

Accordingly, the aim of this CAncer of Rectum REhabilitation Trial (CARRET) study is to evaluate the effectiveness of a pre- and post-surgical pelvic floor rehabilitation program on the bowel symptoms, pelvic floor function, and quality of life of rectal cancer patients up to 3 months after their rehabilitation. The secondary objectives are to assess adherence to home-based PFME and attendance to rehabilitation sessions and to perform intra and intergroup comparisons regarding bowel symptoms and anorectal function considering all time points (baseline, before stoma removal, immediately and 3 months and 1 year after pelvic floor rehabilitation).

**Fig. 1 Fig1:**
[figure not shown]
Flow diagram of the study design

## Methods: participants, interventions, and outcomes

### Study setting {9}

Potential participants will be recruited at Hospital del Salvador, Servicio de Salud Metropolitano Oriente, Santiago de Chile. Evaluations and rehabilitation will be done at the same institution.

### Eligibility criteria {10}

Eligible participants for this study will be adults (aged 18 to 80) with stage I to III rectal cancer who will undergo sphincter preserving surgery at Hospital del Salvador and who have a sufficient understanding of Spanish. They will be recruited at the surgery service for 18 months.

The exclusion criteria will be observed cognitive deficit [mini-mental test score lower than 24] and those patients not meeting criteria for inclusion in the perioperative optimized protocol, such as urgency surgery, neurological diseases like stroke, Parkinson’s or epilepsy, previous gastrectomy, diabetic patient using insulin, renal insufficiency, congestive heart failure, and anesthetic risk ASA 4. Those patients with clinically relevant anastomotic stoma leakage (requiring additional surgical procedures) will be excluded of the study. Neoadjuvant chemoradiotherapy will not be an exclusion criterion.

Interventions will be performed by physical therapists with postgraduation studies on pelvic floor rehabilitation.

### Who will take informed consent? {26a}

The informed consent will be taken from one of the main researchers: CS, LAL, and RS. The process of informed consent will start with a complete explanation of the study, assessments, procedures, risks, and benefits. The patient will have enough time to solve any doubt. Patients will receive a copy of the printed informed consent to carefully read and take it to home for further analysis if they find it necessary.

### Additional consent provisions for collection and use of participant data and biological specimens {26b}

Not applicable.

## Interventions

### Explanation for the choice of comparators {6b}

We decided to compare pre(re)habilitation of the pelvic floor to a control group with standard care without pre(re)habilitation of the pelvic floor because it will give the real benefit of including pelvic floor physiotherapy prior to lower anterior resection for rectal cancer. The study could demonstrate the superiority of starting early pelvic floor rehabilitation.

### Intervention description {11a}

#### Description of the proposed intervention (Fig. 1)

Both groups will receive conventional treatment following institutional perioperative optimized protocol. The pelvic floor intervention for rectal cancer patients will be delivered in two stages: (1) pre-rehabilitation and (2) rehabilitation. Currently, the recommendation is to provide rehabilitation before surgeries in order to prepare patients to improve their functional outcomes. The content of pre-rehabilitation and rehabilitation will include pelvic floor exercises and other techniques aiming at the recovery of pelvic floor maximal function after surgery and the avoidance of low anterior resection syndrome (LARS) symptoms. Pre(re)habilitation will not delay surgical or other treatment times neither interfere in clinical oncological decision-making process.

The pelvic floor intervention, including all stages and techniques, will be provided by a physical therapist with postgraduate studies in pelvic floor treatment and experience in treating rectal cancer patients. This professional will be trained by researchers on the study protocol. The intervention will take place in a private room at Hospital del Salvador.

Stage 1: Pelvic Floor Pre-rehabilitation will be delivered in one session of approximately 40 min with physiotherapist educating on the correct contraction of pelvic floor, teaching pelvic floor muscle exercises, and performing capacitive and sensory training with rectal balloon.

Health education will include the following: the most adequate position for evacuation, self-care strategies such as a high-fiber and low-fat diet that is low in spicy and stimulating food (artificial sweeteners, tea, cola drinks and chocolates), and good bowel habits (the possibility of experiencing an increased urgency to defecate after meal or physical activities).

A booklet was designed for this study with these instructions, and exercises will be provided to the patients as well as an audio that will be sent to their cell phones using the WhatsApp application. The pelvic floor therapist will be given a mobile number with a WhatsApp account so they can send audios and contact patients to reinforce instructions for performing PFME at home. Patients will receive a WhatsApp message once a week to remind them about the exercises. A closer contact with the therapist may increase patients’ self-efficacy and adherence to the treatment [16]. In addition, patients will receive a diary to register the days when they exercise their pelvic floor in order to check adherence to home-based exercises.

Stage 2: Pelvic floor rehabilitation will be delivered in 4 sessions of pelvic floor physiotherapy 3–5 weeks before stoma removal, three times for week. Although anorectal function is not being required for fecal elimination in those with stoma, we will perform PFME and sensory and capacitive training to retrain this function and prevent leakage. In addition, patients will receive 5–8 sessions of pelvic floor physiotherapy starting approximately 2 weeks after stoma removal surgery, over a period of up to 1 month, three times per week, according to patients´ needs. Each session will last approximately 40 min.

Rehabilitation will start around 6–10 weeks after the surgery, depending on physician indication and stoma removal surgery.

The rehabilitation intervention will include pelvic floor exercises, electromyographic biofeedback, and capacitive and sensory training:

Pelvic floor muscle exercises (PFME) will be performed following the protocol of Bø and colleagues [17] who instructed participants to perform a daily total of 24 to 36 slow contractions (high-intensity maximal voluntary contraction with a 6 to 8 s hold). Each slow contraction will be followed by three-to-four fast contractions and then 6 s of rest. In addition, patients will be encouraged to contract the pelvic floor muscles before situations that increase intra-abdominal pressure, known as the “knack” [18]. Patients will be instructed to repeat these exercises at home every day after ostomy removal.

Electromyographic Biofeedback with the equipment Enraf-Nonius Myomed 632X® connected to a large screen for better visualization following a protocol similar to that used by Kuo et al [10] in which neuromuscular stimulation of the pelvic floor muscle was performed 2 to 3 times weekly for a total of 12 treatment sessions. We will use a catheter (Anuform) placed into the anal canal for 10 min during each treatment session. If the patient cannot tolerate the endoanal method, we will use external perineal stimulation. The device delivers a square wave, and ramp up and down time will be set for 2 s with a duration of 8 s at 30 Hz frequency, an on/off time of 1:3, and a pulse duration of 300 ms. Patients will be instructed to actively contract pelvic floor muscles when the electrical stimulus is on.

Capacitive and sensory training with a balloon probe will follow the protocol of Liang et al [9]: a trained therapist will perform repeated inflations and deflations of a balloon in stepwise increments of 5 mL of air or saline solution. The patients will be asked to recognize the volume that induced the urge to defecate and the maximal tolerable volume they were able to hold. The patients will be taught to contract the sphincter in response to the perception of rectal distention. This training will be performed once a week with a duration of approximately 10 min.

Both groups will receive conventional cancer treatment and surgery following perioperative optimized protocols, including 6–10 sessions of multimodal rehabilitation prior to the surgery. It includes physical exercise (aerobic with a stationary bike up to 60–70% of the maximal heart rate reserve calculated with Karnoven et al. (1957) [19] formula and resistance training) and nutritional support. Pre-rehabilitation with physical exercises is recommended by perioperative optimized protocol pathways [3]. A study showed that men with digestive cancers who have a good cardiorespiratory fitness also present a lower risk of mortality [20]. In a large secondary analysis with colorectal cancer patients, authors concluded that multimodal pre-rehabilitation (physical exercise, nutrition, and coping strategies for anxiety) resulted in greater improvement in walking capacity throughout the whole perioperative period when compared to rehabilitation started after surgery [21]. The pre-rehabilitation with physical exercises will be provided by a physical therapist specialized in cancer rehabilitation and trained by researchers on the study protocol. This treatment will be provided at the Service of Physical Medicine and Rehabilitation of Hospital del Salvador.

In case any patient needs adjuvant chemotherapy or radiotherapy, we will wait until the end of these treatments and reassume pelvic floor rehabilitation before ostomy removal. In these cases, patients may take around three additional months to complete treatment.

After completing the follow-up time (3 months) and final evaluations, patients of the control group will be invited to receive 5–10 sessions of pelvic floor rehabilitation.

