### Relevant concomitant care permitted or prohibited during the trial {11d}

Patients can take institutional routine care, including, if necessary, adjuvant chemoradiotherapy. Only patients of the control group will not be allowed to receive pelvic floor physiotherapy during the study period.

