### Provisions for post-trial care {30}

After completing the follow-up time (3 months) and final evaluations, patients of the control group will be invited to receive 5–10 sessions of pelvic floor rehabilitation. No compensation is offered to those who might suffer from harm from trial participation. However, we are negotiating an insurance contract to better protect patients.

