### Outcomes {12}

Evaluations will take place at baseline (T1), around 3–5 weeks before stoma removal and before rehabilitation (T2), immediately after rehabilitation (T3), 3 months (T4), and 1 year after rehabilitation (T5).

The primary outcomes are the mean score of bowel symptoms and the mean score of anorectal function. The primary time point will be 3 months after finishing pelvic floor rehabilitation treatment.

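### Controls are offered rehabilitation after 3 months, so the 1-year comparison is early versus deferred treatment; and T3 to T5 are dated from a treatment that controls do not receive

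*Protocol article*

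**What the plan says.** All references are to the protocol article.

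- **Offer to controls.** Description of the proposed intervention: "After completing the follow-up time (3 months) and final evaluations, patients of the control group will be invited to receive"; what is offered is a pelvic floor course of 5–10 sessions. Provisions for post-trial care {30} repeats the sentence, again with 3 months in brackets.
- **1-year comparison.** Objectives {7} sets as a secondary aim to "perform intra and intergroup comparisons regarding bowel symptoms and anorectal function considering all time points", and its list of time points includes 1 year after rehabilitation. Outcomes {12} schedules that visit as T5.
- **Restriction on controls.** Relevant concomitant care {11d}: "Only patients of the control group will not be allowed to receive pelvic floor physiotherapy during the study period".
- **Visit dates.** Outcomes {12} places T2 around 3–5 weeks before stoma removal. T3, T4 and T5 are placed immediately, 3 months and 1 year after rehabilitation. "The primary time point will be 3 months after finishing pelvic floor rehabilitation treatment", which is T4.
- **Control treatment.** Trial design {8} gives controls conventional treatment only.
- **Length of the course.** After stoma removal the experimental arm has 5–8 sessions, three a week, within at most a month and according to need.

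**The concern.** Two separate problems arise.

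**The meaning of T5.** If controls may start rehabilitation after the 3-month visit, some will have had it by 1 year. The Discussion frames the trial as rehabilitation against none, and a reader will take the T5 result in that sense. A null result at T5 could then be reported as a benefit that faded, when the control arm may simply have caught up. The sections also disagree about when the study period ends for controls.

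**The date of T3, T4 and T5.** These visits are defined by an event that only one arm has and whose date depends, within that arm, on how many sessions a patient needs. The background section says "LARS can show improvement over the first 2 years", so symptoms may change with time whatever the treatment. If control visits are not matched, the arms would be measured after different lengths of recovery, and that difference would be mixed with the treatment effect. This reaches T4, the primary time point.

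**Working it through.** **1. The sections side by side.** There are two ways to read the study period for controls.

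- *It runs to T5.* The bar in {11d} then contradicts the offer at 3 months, which is stated twice.
- *It ends at 3 months.* The bar and the offer agree, but the between-group comparison at T5 in {7} falls outside the period in which the contrast with no rehabilitation is protected.

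Reading the final evaluations as T5 would remove the conflict with {11d}, but it does not fit the 3 months in brackets. On every reading some text must change.

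**2. The plan's own figure.** Sample size {14} gives means of 2.8 (SD 2.8) and 4.9 (SD 5.7), power 80% and alpha 0.05, and reports 56 in total. The difference is 4.9 − 2.8 = 2.1. Per arm, two-sided:

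n = 2 × (1.960 + 0.842)² × (2.8 / 2.1)² = 2 × 7.85 × 1.778 = 27.9, so 28 per arm and 56 in total.

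The figure reproduces only with SD 2.8 in both arms. With both stated SDs the root mean square is √[(2.8² + 5.7²)/2] = 4.491. The point below does not depend on which SD is used, so both are shown.

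**3. Dilution at T5.** Let u be the share of controls who take up the offer and e the share of the full effect that they gain. The documents give neither, so both are assumed. Expected difference = 2.1 × (1 − u × e). Power, with 28 per arm, is Φ(difference / [SD × √(2/28)] − 1.96).

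| u | e | Difference | Power, SD 2.8 | Power, SD 4.491 |
|---|---|---|---|---|
| 0 | any | 2.10 | 80% | 42% |
| 0.5 | 0.5 | 1.58 | 56% | 26% |
| 0.5 | 1 | 1.05 | 29% | 14% |
| 0.75 | 1 | 0.53 | 10% | 6% |
| 1 | 1 | 0 | alpha level | alpha level |

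**4. Timing of T4.** The course after stoma removal starts about 2 weeks (intervention description) or about 3 weeks (abstract) after that surgery; the two statements need reconciling.

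- Earliest end: 2 + 5/3 = 3.7 weeks (5 sessions at three a week).
- Latest end at three sessions a week: 3 + 8/3 = 5.7 weeks.
- Latest end if the full month is used: 3 + 4.3 = 7.3 weeks.

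Adding 13 weeks, T4 in the experimental arm falls about 16.7 to 20.3 weeks after stoma removal, a spread of 3.6 weeks within that arm alone. For controls the text gives no date. If their visits are matched to the experimental arm, the gap is zero. If they were seen 13 weeks after stoma removal, the gap would be 3.7 to 7.3 weeks. The second case is an assumption that nothing in the documents supports.

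**The case against.** **On T5.** The main aim and the primary time point stop at 3 months after rehabilitation, and the offer comes later, so only a secondary comparison is affected. The offer also stands under post-trial care, which suggests that the authors regard the protected period as over. This is right, and it limits the point to T5.

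A reader might infer that T5 is no longer a randomised comparison. That does not follow. The groups are still compared as randomised; the offer changes the question from rehabilitation versus none to early versus deferred. The comparator section itself speaks of the superiority of starting early.

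A reader might also fear a spurious 1-year benefit. If deferred rehabilitation helps controls, the bias runs towards the null. The table is illustrative too: 2.1 is a pilot difference after rehabilitation, not a 1-year effect. Equal benefit is a strong assumption, because controls would have 5–10 sessions without the pre-surgical one, against one plus 9–12.

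**On the visit dates.** The flow diagram and the SPIRIT schedule are not shown and may give control visit times, and a journal article may leave visit windows to the full protocol. It is therefore tempting, but unsupported, to say that the experimental arm has several extra weeks of recovery at T4. Nor does the background section name stoma removal as the start of recovery; it says only that symptoms can improve over 2 years, and gives no rate. What stands is that the written definition of the primary time point rests on an event that controls do not have.

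**Conclusion.** Both parts hold within limits.

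1. Taken with the stated 3 months, the T5 between-group comparison estimates early versus deferred (offered) rehabilitation. It is probably diluted, by an amount that depends on uptake and benefit that the documents do not give: from 2.1 to 1.58 or 1.05 in the two middle cases, and to zero at the extreme. It cannot be read as lasting benefit over no rehabilitation. The T4 comparison is unaffected by the offer.
2. T3, T4 and T5 have no stated date in the control arm, and a date that varies with need in the experimental arm. If control visits are unmatched, time since stoma removal is confounded with treatment, including at the primary time point. Whether there is a gap, and what it is worth in score points, the documents do not show.

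**What to change.** - Reconcile Objectives {7}, the intervention description {11a}, concomitant care {11d}, post-trial care {30} and Outcomes {12}, so that the end of the study period for controls and the status of T5 are stated once and consistently.
- State that T4 is the last comparison against no rehabilitation. Keep T5 as a comparison of the groups as randomised, and interpret it as early versus deferred rehabilitation.
- Record, for each control, whether the offer was taken up and the number of sessions received before T5.
- Define T3, T4 and T5 in both arms by the same windows counted from the date of stoma removal, which T2 already uses, with T3 set after the longest permitted course. If the figures or the full protocol already fix matched control visits, bring Outcomes {12} into line with them.

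The cost is wording, visit scheduling and one added data item. Recruitment had not begun when the article was written. What is given up is any reading of T5 as superiority over no rehabilitation. None of these changes requires altering the offer to controls.
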